#### Exclusion of Data from Analysis

The following patients will be excluded from the standard (per protocol) analysis:

1. Patients who never took any study medication.
2. Patients on PEGASYS® who received ≤80% of both planned PEGASYS®  and COPEGUS® dose for ≤80% of planned treatment duration.
3. Patients with no post-baseline HCV-RNA assessment.

The following patients will be excluded from the safety analysis:

1. Patients who never took any study medication.
2. Patients without any post-baseline safety assessment.

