In the event of ribavirin being discontinued, the patient may continue to receive PEG-IFN alfa-2a monotherapy for the rest of the planned treatment period. Ribavirin can be reintroduced, at the investigator´s discretion. Ribavirin may be reintroduced at full dose or in a stepwise manner as indicated in the table above.

The use of erythropoietin (NeoRecormon) ≥3000 IE 3 times week sc is permitted throughout the study at the discretion of the treating physician with the exception if the patient has any of the following exclusion criteria for the use of erythropoietin: platelet count >500,000, risk of thrombosis, or poorly controlled hypertension, especially if hemoglobin decreases persistently to < 10.0 g/dL or in the event of a rapid decrease in hemoglobin exceeding 4.0 g/dL over a 2 week period. If erythropoietin is initiated, a new ribavirin concentration at local lab should be evaluated after 4 weeks in Groups A (“Loading”) and B (“Priming”).

In the event of anemia, dose reductions of ribavirin are permitted in all study arms throughout the study at the discretion of the treating physician.

If hemoglobin decreases to < 8.0 g/dL, ribavirin should be discontinued.

If hemoglobin decreases to < 7.0 g/dL, blood transfusion should be considered at the discretion of the treating physician.

If hemoglobin decreases to < 6.5 g/dL, blood transfusion should be given.

If any dose of ribavirin dosing is missed (or changed), that information must be recorded on the Case Report Form.

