#### Adverse Reaction

The primary toxicity of ribavirin is anemia. Reduction in hemoglobin levels generally occurs within the first 1-2 weeks of initiating therapy. Cardiac and pulmonary events associated with anemia may occur.

Ribavirin should be administered with caution to patients with pre-existing cardiac disease. Patients should be assessed before commencement of therapy and should be appropriately monitored during therapy. If there is any deterioration of cardiovascular status, therapy should be stopped. Ribavirin should be administered with additional precautionary statement for diabetic patients and patients with history of gout to increase the safety of test drug administration

In addition, ribavirin is contraindicated in patients with a history of hypersensitivity to ribavirin.

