## Statistical and Analytical Methods

### Analysis Plan

This is a pilot trial with the viral kinetic response and SVR measured as described above, during the first 12 weeks of therapy as primary endpoint with the aim of investigating the feasibility and safety of “loading” and “priming” dosing of ribavirin in conjunction with PEG-IFN for chronic HCV genotyp 1. Intention-to-treat and Per-protocol analysis on primary endpoints will be performed for patients receiving at least one dose of the study drugs. Additionally, an analysis of SVR with regards to whether or not the target concentration of ribavirin 2.5 mg/L (10.25 μmol/L) at day 28 was achieved across all study arms will be performed.

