#### Definition of Analysis Populations

**Intent-to-treat analysis population** is defined to include all patients who received at least one dose of study medication. Except for change from baseline parameters, the primary and all other secondary efficacy parameters will be analyzed using the intent-to-treat population.

**Per-protocol** **analysis population** is defined to include all patients who received ≥80% of both planned Pegasys and Copegus dose for ≥80% of planned treatment duration.

**Standard analysis (per-protocol) population** will exclude a patient if the patient meets any of the exclusion criteria listed in Section 9.2.2.2. Analysis using the standard population will be performed only if > 5% of patients are excluded from one of the treatment groups.

**Safety analysis population** is defined to include only patients who receive at least one dose of (either) study medication and have at least one post-baseline safety assessment.

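### Protocol Sections 9.2.1.1 and 9.2.1.2 give two per-protocol rules that are not complements: one drops a patient who misses any 80% criterion, the other only a patient who misses all three.

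*Protocol*

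**What the plan says.** Section 9.2.1 (Analysis Plan) states: "Intention-to-treat and Per-protocol analysis on primary endpoints will be performed". It does not describe the per-protocol set further.

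Section 9.2.1.1 (Definition of Analysis Populations) then names two sets that both carry the per-protocol label:

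- The per-protocol population is "all patients who received ≥80% of both planned Pegasys and Copegus dose for ≥80% of planned treatment duration".
- The standard (per-protocol) population is defined by an exclusion list. The text places that list in Section 9.2.2.2, but by the table of contents it is in 9.2.1.2. This set has a condition on its use: "Analysis using the standard population will be performed only if > 5% of patients are excluded from one of the treatment groups".

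Item 2 of the list in Section 9.2.1.2 (Exclusion of Data from Analysis) is one sentence that begins "Patients on PEGASYS® who received ≤80% of both planned PEGASYS" and ends "COPEGUS® dose for ≤80% of planned treatment duration". Items 1 and 3 cover patients who took no study medication and patients without an HCV-RNA result after baseline.

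**The concern.** Item 2 reads as the reverse of the 9.2.1.1 rule, but only the inequality signs were turned round. The opposite of being at or above 80% on both drugs and on duration is being below 80% on either drug or on duration. By keeping 'both' and the conjunction, item 2 excludes almost nobody whom 9.2.1.1 would drop for a single shortfall.

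The gap falls on a group that matters here. The trial compares ribavirin dosing strategies, and Section 8.5.2.3 says "The primary toxicity of ribavirin is anemia". Ribavirin may be reduced for anemia in every arm. Section 8.3.2 adds: "In the event of ribavirin being discontinued, the patient may continue to receive PEG-IFN alfa-2a monotherapy for the rest of the planned treatment period". A shortfall on ribavirin alone is therefore foreseen. Group A takes a double dose for two weeks, so such cases need not be balanced across arms.

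A per-protocol set that keeps patients who took a small fraction of their ribavirin does not answer a per-protocol question about ribavirin dosing. In an open-label trial, having two rules to choose from also leaves room to choose after the data have been seen.

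**Working it through.** The protocol states no figure to reproduce. The check compares the two rules.

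**Inputs.** The inclusion rule is in 9.2.1.1, item 2 is in 9.2.1.2, arm size is 35 (Section 3.2), and dosing is from Section 3.1 and Appendix 3.

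**Step 1: the eight patterns.** Treat each criterion as met or missed, away from the 80% boundary.

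| PEGASYS dose | Copegus dose | Duration | 9.2.1.1 | Item 2 as written | Item 2, 'both' read as 'either' |
| --- | --- | --- | --- | --- | --- |
| met | met | met | in | in | in |
| met | met | missed | out | in | in |
| met | missed | met | out | in | in |
| met | missed | missed | out | in | out |
| missed | met | met | out | in | in |
| missed | met | missed | out | in | out |
| missed | missed | met | out | in | in |
| missed | missed | missed | out | out | out |

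9.2.1.1 keeps 1 pattern. Item 2 as written keeps 7, so they disagree on 7 − 1 = 6 of 8. With 'either', item 2 keeps 5, so they disagree on 5 − 1 = 4 of 8. The patient who misses only the Copegus dose is among those 4.

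The patterns are not equally likely. If dose is counted cumulatively against the whole plan, a short duration lowers both doses too, and patterns with duration missed but a dose met become rare. The three with duration met and a dose missed do not depend on this.

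**Step 2: the boundary.** A patient at exactly 80% on all three is in under 9.2.1.1 (≥80%) and excluded under item 2 (≤80%). Over a grid of 70, 80 and 90% on each criterion (27 profiles), the rules disagree on 13. Suppose item 2 is read most loosely, so that ≤80% on either drug or on duration excludes. The ribavirin-only conflict then goes, but 7 of 27 profiles still conflict, all involving a value of exactly 80%.

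**Step 3: ribavirin stopped at week 4 of combination therapy, PEGASYS completed, 48-week plan.** The unit is one week of maintenance dose; Group A's first two weeks count double, and Group B has four priming weeks.

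- Group C: 4 / 48 = 8.3%
- Group A: (2 × 2 + 2) / (2 × 2 + 46) = 6 / 50 = 12.0%
- Group B: (4 + 4) / (4 + 48) = 8 / 52 = 15.4%

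All are far below 80%, so the patient is out under 9.2.1.1. PEGASYS is at 100%, so item 2 as written cannot apply and the patient is in. This holds whether dose is counted cumulatively or as a level held over time.

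**Step 4: the >5% condition.** 1 / 35 = 2.9% and 2 / 35 = 5.7%, so two exclusions in an arm trigger the standard analysis. Ribavirin-only shortfalls add none under item 2. They could be common in an arm and still not trigger it.

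**The case against.** The protocol may intend two sets. Read by name, 9.2.1 promises the per-protocol analysis and the >5% condition attaches only to the standard population, so both can be followed. That stands: there is no contradiction over whether a per-protocol analysis is run. It does not rescue item 2. Both sets are labelled per-protocol, share the 80% thresholds and are given no separate purpose.

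The effect is also limited. This is a pilot. The sample-size contrasts are day 0 to 3 and day 7 to 28, and the primary window closes at week 12. Later ribavirin reductions change who is in the set, not those measurements. This too stands.

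Three stronger readings are tempting, and the document does not support them.

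- A reader might infer that the primary endpoint lacks intention-to-treat cover, because 9.2.1.1 says: "Except for change from baseline parameters, the primary and all other secondary efficacy parameters will be analyzed using the intent-to-treat population". The exception is loosely worded, but 9.2.1 expressly promises intention-to-treat analysis of the primary endpoints.
- A reader might infer that a modest dose step lasting some weeks moves a patient between the sets. That depends on whether dose is cumulative or a level held over time, which the text does not settle. On a cumulative count, a step to 75% takes the total below 80% only if 0.25 × t / 48 > 0.20, so t > 38.4 of 48 weeks. Group B's Copegus course is 28 or 52 weeks and would need its own figures.
- A reader might infer that week-12 non-responders are certainly dropped by 9.2.1.1. That holds only if planned duration means 48 weeks (12 / 48 = 25%). If it means the duration the protocol directs for that patient, a full-dose patient meets it.

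**Conclusion.** The point holds as a faulty negation in item 2 of 9.2.1.2, which leaves two incompatible per-protocol rules: 6 of 8 patterns in conflict as written, 4 of 8 on the 'either' reading, plus the exact-80% case. The ribavirin-stop example needs only the Appendix 3 dose as the planned dose and a 48-week plan. How many patients would be affected cannot be derived. The effect is confined to the per-protocol analysis and to the trigger for the standard one. This is not a detail left to a statistical analysis plan, because such a plan would have to contradict one of the two sections. It should be corrected, but it does not threaten the intention-to-treat result.

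**What to change.** Rewrite item 2 of Section 9.2.1.2 as: *Patients who received <80% of planned PEGASYS dose, or <80% of planned Copegus dose, or were treated for <80% of planned duration.* On dose and duration this is the exact complement of the 9.2.1.1 rule, including at 80%. Use it as the single per-protocol rule, so that the separate standard population and its >5% condition are no longer needed, and correct the cross-reference in 9.2.1.1 from 9.2.2.2 to 9.2.1.2.

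Add that patients stopped under the week-12 or week-24 stopping rule (Section 7.5) count as having completed planned duration, with planned dose counted to that stop. Otherwise, if planned duration is read as 48 weeks, the per-protocol set would drop patients stopped at week 12 because their primary outcome was poor.

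The cost is a few sentences, written before the per-protocol set is fixed. No new data are needed, because missed, reduced or changed doses are already recorded in the CRF (Sections 7.4 and 8.3).

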#### Safety Data Analysis

Adverse events will be assigned preferred terms and categorized into body systems according to the Medical Dictionary for Drug Regulatory Affairs (MedDRA) classification of the World Health Organization (WHO) terminology. In the analyses adverse events occurring during treatment and within 168 days of last trial medication will be summarized.

The proportion of patients with reported adverse events during the target period, will be calculated by dividing the number of these patients by the number of patients that can be evaluated for safety. Adverse events will be summarized by study groups mentioned in Section 9.2.2.1, by body system and event within each body system.

Certain potentially clinically relevant laboratory abnormalities will be analyzed in more detail. These laboratory abnormalities include anemia, neutropenia, thrombocytopenia, and elevated ALT levels.

For hemoglobin, neutrophil and platelet counts the lowest value for each patient during treatment and follow-up will be summarized.

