### Ribavirin Dose Modifications

If the ribavirin concentration measured on day 28 in Groups A and B is below the target concentration (2.5 mg/L (10.25 mol/L)), the dose of ribavirin should be increased as soon as possible preferably within 2 weeks of measuring the ribavirin concentration if the patient can tolerate an increase. The new recommended dose is the previously given dose divided by the concentration of ribavirin measured multiplied by the target concentration (2.5 mg/L (10.25 mol/L)) (see Appendix 3).In the event of a change in ribavirin dosing in Groups A (“Loading”) and B (“Priming”), a new local ribavirin concentration should be evaluated after 4 weeks. Ribavirin should be administered twice-daily with food.

Where dose reduction is required stepwise incremental adjustments of 200 mg (1 tablet) should be utilized where clinical circumstance allows.

If either of the following is confirmed, it is recommended that the ribavirin dose should be reduced, at the discretion of the investigator dependent on local treatment guidelines:

- A patient without significant cardiovascular disease experiences a fall in hemoglobin to <10 g/dL (<100 g/L) and >8.5 g/dL (>85 g/L) or
- A patient with stable cardiovascular disease experiences a fall in hemoglobin by >2 g/dL (>20 g/L) during any 4 weeks of treatment

For the purposes of this protocol, patients with “stable cardiovascular disease” include not only patients with known, stable cardiac and vascular disorders, but also patients with major cardiac risk factors including hypertension and diabetes mellitus.

Patients who have more than a 3 g/dL (30 g/L) decrease from baseline in their Hgb concentration should have an appropriate work-up for anemia, including reticulocyte count, search for sources of bleeding, etc.

Moreover, ribavirin should be discontinued under the following circumstances:

- If a patient without significant cardiovascular disease experiences a fall in hemoglobin confirmed to be less than 8.0 g/dL (80 g/L).
- If a patient with stable cardiovascular disease maintains a hemoglobin value <12 g/dL (<120 g/L) despite 4 weeks on a reduced dose of 600 mg.

Ribavirin monotherapy is not allowed; in the event that PEG-IFN alfa-2a treatment has to be permanently discontinued the patient must cease all study medications and must be followed for safety reasons for at least 12 weeks.

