### SVR rate and percentage of patients with normal serum ALT levels at 24 weeks after completion of the treatment period in the total patient population, and its association with the following factors:

### early virological response

### pharmacokinetic response to ribavirin

### Secondary Safety Variables

- Adverse event rate and profile
- Other laboratory tests
- The proportion of patients experiencing anemia grade 1 (10.5-9.5 g/dL), grade 2 (9.4-8.0 g/dL), grade 3 (7.9-6.5 g/dL), and grade 4 (< 6.5 g/dL) will be evaluated in each study arm.

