#### Interim Analysis

# An independent DSMB will evaluate safety after the first 30 patients have reached treatment weeks 2 and 12.

## Sample Size

This is a pilot trial with the viral kinetic response and SVR measured as described above, during the first 12 weeks of therapy as primary endpoint with the aim of investigating the feasibility and safety of “loading” and “priming” dosing of ribavirin in conjunction with PEG-IFN for chronic HCV genotyp 1. To demonstrate an increase in the reduction of HCV RNA from day 0 to 3 from 0.9 log10 IU/mL in Group C (Standard-of-Care) to 1.4 log10 IU/mL in Group A or B or an increase in the reduction of HCV RNA from day 7 to 28 from 0.4 log10 IU/mL/week in Group C (Standard-of-Care) to 0.6 log10 IU/mL/week in Group A or B the study requires at least 35 patients per study arm. The statistical power (chance) for the study to detect a superior effect in Group A or B as compared to C is 80%. Statistical sample-size calculation is based on z-test for differences between proportions and is one-sided with a significance level of 5%.

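### The haemoglobin summaries the protocol defines capture neither the size nor the timing of an early fall, so they could miss or misattribute an effect of the 2-week loading dose

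*Protocol*

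**What the plan says.** Two haemoglobin summaries are spelled out in the protocol. Section 9.2.1.3 (Safety Data Analysis) states: "For hemoglobin, neutrophil and platelet counts the lowest value for each patient during treatment and follow-up will be summarized". Section 9.1.3 (Secondary Safety Variables) lists, per arm, "The proportion of patients experiencing anemia grade 1 (10.5-9.5 g/dL), grade 2 (9.4-8.0 g/dL), grade 3 (7.9-6.5 g/dL"), with grade 4 below 6.5 g/dL.

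Three looser provisions stand beside them. Section 9.2.1.3 says "Certain potentially clinically relevant laboratory abnormalities will be analyzed in more detail" and names anaemia among these, without saying what the analysis is. Section 9.1.3 lists "Other laboratory tests". Section 9.2.1.4 says "An independent DSMB will evaluate safety after the first 30 patients have reached treatment weeks 2 and 12".

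Other sections deal with the size and timing of a fall. Section 8.5.2.3 calls anaemia the primary toxicity of ribavirin and adds "Reduction in hemoglobin levels generally occurs within the first 1-2 weeks of initiating therapy". Section 8.3.2 mentions erythropoietin especially for persistently low haemoglobin or "in the event of a rapid decrease in hemoglobin exceeding 4.0 g/dL over a 2 week period". It also says "Patients who have more than a 3 g/dL (30 g/L) decrease from baseline in their Hgb concentration should have an appropriate work-up for anemia". Section 7.1 gives Group A twice the ribavirin dose for the first 2 weeks, and section 9.3 names feasibility and safety of loading and priming as the aim of the pilot.

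**The concern.** The safety question specific to loading is what happens to haemoglobin while the double dose is taken and shortly afterwards. A lowest value over the whole course carries no date. An absolute grade ignores where the patient started. If Group A fell faster in weeks 0-2 but the arms reached similar lowest values later, both summaries could look alike in A and C. Conversely, a lower nadir in A that arose after a later ribavirin increase could be read as an effect of loading.

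A protocol is free to leave laboratory tables to the analysis plan. Here it names particular summaries, and those do not fit the question the pilot asks.

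**Working it through.** The protocol gives no haemoglobin target difference, SD or power, so there is no figure to reproduce. The check has four parts.

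**1. Falls that the grades do not register.** Inputs: grade 1 starts at 10.5 g/dL (9.1.3); screening haemoglobin must be at least 12 g/dL in women and 13 g/dL in men (4.3). A fall of d is ungraded if baseline − d > 10.5, that is, if baseline > 10.5 + d.
- d = 4.0: baseline above 10.5 + 4.0 = 14.5 g/dL.
- d = 3.0: baseline above 10.5 + 3.0 = 13.5 g/dL.
- Example: 15.5 − 4.5 = 11.0 g/dL. This passes both fall thresholds in 8.3.2 and has no grade.
- At the eligibility floors, a woman is grade 1 after losing 12.0 − 10.5 = 1.5 g/dL and a man after 13.0 − 10.5 = 2.5 g/dL.

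So a small fall can be graded and a large one ungraded.

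**2. Adverse event tables.** Section 8.1.2 lets anaemia be reported as an adverse event only below 8.5 g/dL. The patient at 11.0 g/dL is 2.5 g/dL above that limit and does not appear there either.

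**3. What the whole-course lowest value mixes together.**
- Length: planned treatment is 24, 48 or possibly 72 weeks in A and C, and 28, 52 or possibly 76 in B, plus 24 weeks of follow-up (3.1). The window runs from 24 + 24 = 48 to 76 + 24 = 100 weeks, and is shorter for patients stopped at week 12. It depends on arm and on virological response.
- Later dosing: ribavirin may be raised towards 2.5 mg/L after the day-28 concentration in A and B, but not in C (7.1, 8.3.2, Appendix 3).
- Rescue: erythropoietin and dose reduction are at the physician's discretion in an open-label trial (8.3.2). A steep early fall can prompt action that changes the later nadir.

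**4. Illustration of the possible loss.** All haemoglobin values here are assumptions, not protocol figures: mean fall 3.0 g/dL in both arms by weeks 8 and 12; week-4 fall 3.0 in A and 2.6 in C; between-patient SD 1.0; within-patient SD 0.5; 35 per arm; two-sided 5% test. The SD of a single-visit fall is √(1.0² + 0.5²) = 1.12. For a 1.0 g/dL difference at week 2 the standard error is 1.12 × √(2/35) = 0.27, which gives power of about 96%. The nadir results come from simulating the largest fall over the four visits.

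| Assumed week-2 fall, A / C (g/dL) | Week-2 difference | Power | Difference in largest fall | Power |
|---|---|---|---|---|
| 2.5 / 1.5 | 1.0 | 96% | 0.11 | 6% |
| 3.0 / 2.0 | 1.0 | 96% | 0.18 | 11% |
| 3.0 / 1.5 | 1.5 | >99% | 0.18 | 11% |

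The model leaves out dose targeting, erythropoietin and baseline spread. It shows what can happen if later falls converge, not what will happen.

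**The case against.** The strongest reply is that this asks for extra tables and shows no wrong figure or contradiction. The protocol promises a closer analysis of anaemia, lists other laboratory tests as a safety variable, and has a DSMB look at week 2, when loading ends. By-visit and change-from-baseline tables usually belong in the analysis plan, which is not shown. Most action thresholds are also absolute (below 10, 8.0, 7.0 and 6.5 g/dL), so the grades match much of the management scale.

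Much of this stands, and it rules out several stronger readings:
- A reader might infer that the early fall will go unreported. That cannot be established: the closer analysis is undefined and the analysis plan may add tables.
- A reader might infer that the safety comparison will be wrong. Nadir and grade are valid summaries; they answer a different question.
- A reader might infer that all arms take the same ribavirin dose after week 2. Concentration targeting in A and B contradicts that.
- A reader might infer that every fall criterion covers all patients. The rule of more than 2 g/dL in 4 weeks is for stable cardiovascular disease, and the eligibility text on an acute 4 g/dL fall is for coronary or cerebrovascular disease.
- A reader might infer that the protocol predicts a larger fall with loading. Section 8.5.2.3 speaks of ribavirin in general; the larger fall is an inference from the doubled dose.

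What the reply does not do is show a commitment to compare the early fall between arms. The DSMB review covers 30 patients, about 30/3 = 10 per arm if balanced, and is not a final comparison. The closer analysis has no stated content.

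**Conclusion.** The point holds as a weakness in the chosen summaries. Neither summary that the protocol defines measures the size or timing of an early haemoglobin fall, although safety of loading is a declared aim and the double dose coincides with the weeks in which the protocol expects falls. Falls of 4.0 g/dL from above 14.5 g/dL, or 3.0 g/dL from above 13.5 g/dL, are ungraded. The whole-course lowest value cannot separate loading from later targeting, rescue and treatment length.

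The threshold arithmetic rests only on protocol figures. How many patients start above 14.5 g/dL is unknown, because no baseline distribution is given. The power contrast (96% or more against 6-11%) rests entirely on the stated assumptions, chiefly that later falls are equal. An early effect could be missed or misattributed; nothing shows that it will be.

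**What to change.** Keep the nadir and grade tables. In sections 9.1.3 and 9.2.1.3 add, by arm and timed from the first ribavirin dose:
- change in haemoglobin from the pre-ribavirin value to about week 2 and week 4;
- the lowest value in the first 4 weeks of ribavirin;
- the proportions with a fall of more than 4.0 g/dL over 2 weeks and of more than 3 g/dL from baseline.

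The ribavirin clock matters for Group B, which starts ribavirin at day -28. A baseline taken at the first interferon dose would already include four weeks of ribavirin. Appendix 5 ties day 0 both to the first interferon dose and to the first study medication, so the reference day should be written out. In those weeks B takes ribavirin alone, so its comparison with A and C describes whole regimens.

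Use haemoglobin samples already scheduled. The visit table is not in the text reviewed. The day-14 samples that can be seen are for ribavirin and IP-10, and in Group B the visible priming samples are at days -28, -27 and -21, for virology and ribavirin. Haemoglobin timing therefore needs checking. If B has no haemoglobin at ribavirin week 2, compare the three arms at the nearest common ribavirin time, such as day 28, and compare A with C at week 2.

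The cost is a few more descriptive tables. No dose or clinical rule changes.
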